### 8.1.2 Serious Adverse Events

Investigators should report all AEs that meet the definition of an SAE (see Appendix 3 for definition).

#### 8.1.2.1 Monitoring pregnancies for potential Serious Adverse Events

It is important to monitor the outcome of pregnancies of patient's partners in order to provide SAE data on congenital anomalies or birth defects.

In the event that a patient's partner becomes pregnant during the SAE reporting period please complete a Pregnancy Notification Form (providing the patient's details) and return to the Trials Office as soon as possible. The patient should be given a Release of Medical Information Form to give to their partner. If the partner is happy to provide information on the outcome of their pregnancy they should sign the Release of Medical Information Form. Once consent has been obtained provide details of the outcome of the pregnancy on a follow-up Pregnancy Notification Form and if necessary also complete an SAE Form.

### 8.1.3 Reporting period

Details of all AEs (except those listed above) will be documented and reported from the date of commencement of protocol defined treatment until 28 days after the administration of the last treatment. SAEs that are judged to be at least possibly related to tamoxifen must still be reported in an expedited manner irrespective of how long after IMP administration the reaction occurred. Special attention should be paid to women who develop endometrial problems.

## 8.2 Reporting Procedure

### 8.2.1 Site

#### 8.2.1.1 Adverse Events

AEs should be reported on an AE Form (and where applicable on an SAE Form). The AE Form is a continuous form completed via the eCRF. The form should be checked and updated as applicable at each visit.

AEs will be reviewed using the CTCAE version 4.0 (see Appendix 4). Any AEs experienced by the patient but not included in the CTCAE should be graded by an Investigator and recorded on the AE Form using a scale of (1) mild, (2) moderate or (3) severe. For each sign/symptom, the highest grade observed since the last visit should be recorded.

#### 8.2.1.2 Serious Adverse Events

For more detailed instructions on SAE reporting refer to the SAE Form Completion Guidelines contained in the Investigator Site File (ISF).

AEs defined as serious and which require reporting as an SAE (excluding events listed in Section 8.1 above) should be reported on an SAE Form. When completing the form, the Investigator will be asked to define the causality and the severity of the AE which should be documented using the CTCAE version 4.0.

On becoming aware that a patient has experienced an SAE, the Investigator (or delegate) must complete, date and sign an SAE Form. The form should be faxed together with a SAE Fax Cover Sheet to the Trials Office using one of the numbers listed below as soon as possible and no later than 24 hours after first becoming aware of the event:

To report an SAE, either e-mail or fax the SAE Form with an SAE Fax Cover Sheet to:

**[name] or [name] Or [[contact]](mailto:[contact])**

On receipt the Trials Office will allocate each SAE a unique reference number. This number will be transcribed onto the SAE Fax Cover Sheet which will then be faxed or e-mailed back to the site as proof of receipt. If confirmation of receipt is not received within 1 working day please contact the Trials Office. The SAE reference number should be quoted on all correspondence and follow-up reports regarding the SAE. The SAE Fax Cover Sheet completed by the Trials Office should be filed with the SAE Form in the ISF.

For SAE Forms completed by someone other than the Investigator the Investigator will be required to countersign the original SAE Form to confirm agreement with the causality and severity assessments. The form should then be returned to the Trials Office in the post and a copy kept in the ISF.

Investigators should also report SAEs to their own Trust in accordance with local practice.

### 8.2.1.3 Provision of follow-up information

Patients should be followed up until resolution or stabilisation of the event. Follow-up information should be provided on a new SAE Form (refer to the SAE Form Completion Guidelines for further information).

### 8.2.2 Trials Office

On receipt of an SAE Form seriousness and causality will be determined independently by a Clinical Coordinator. An SAE judged by the Investigator or Clinical Coordinator to have a reasonable causal relationship with the trial medication will be regarded as a Serious Adverse Reaction (SAR). The Clinical Coordinator will also assess all SARs for expectedness. If the event meets the definition of a SAR that is unexpected (i.e. is not defined in the Reference Safety Information (RSI)) it will be classified as a Suspected Unexpected Serious Adverse Reaction (SUSAR).

### 8.2.3 Reporting to the Competent Authority and main Research Ethics Committee

#### 8.2.3.1 Suspected Unexpected Serious Adverse Reactions

The Trials Office will report a minimal data set of all individual events categorised as a fatal or life threatening SUSAR to the Medicines and Healthcare products Regulatory Agency (MHRA) and main Research Ethics Committee (REC) within 7 days. Detailed follow-up information will be provided within an additional 8 days.

All other events categorised as SUSARs will be reported within 15 days.

#### 8.2.3.2 Serious Adverse Reactions

The Trials Office will report details of all SARs (including SUSARs) to the MHRA and main REC annually from the date of the Clinical Trial Authorisation, in the form of a Development Safety Update Report (DSUR).

#### 8.2.3.3 Adverse Events

Details of all AEs will be reported to the MHRA on request.

#### 8.2.3.4 Other safety issues identified during the course of the trial

The MHRA and main REC will be notified immediately if a significant safety issue is identified during the course of the trial.

### 8.2.4 Investigators

Details of all SUSARs and any other safety issue which arises during the course of the trial will be reported to Principal Investigators. A copy of any such correspondence should be filed in the ISF.

### 8.2.5 Trial Steering Committee

The independent Trial Steering Committee (TSC) will review all SAEs.

## 9. DATA HANDLING AND RECORD KEEPING

### 9.1 Data Collection

The electronic Case Report Form (eCRF) will comprise, but is not limited to, the following forms:

| Form                  | Summary of data recorded    | Schedule for submission         |
|-----------------------|-----------------------------|---------------------------------|
| Eligibility Checklist | Confirmation of eligibility | Completed prior to registration |

|                                       |                                                                                                                                       |                                                  |
|---------------------------------------|---------------------------------------------------------------------------------------------------------------------------------------|--------------------------------------------------|
| Registration                          | Patient details                                                                                                                       | Completed as part of registration                |
| Baseline                              | Medical history, previous treatment, baseline characteristics, haematology/biochemistry assessments and details of medical exam       | Within 2 weeks of registration                   |
| Treatment Form                        | Treatment details, haematology/biochemistry assessments and details of medical exam                                                   | Within 2 weeks of scheduled visit                |
| Treatment Form – Week 24              | Treatment details, haematology/biochemistry assessments, details of medical exam and bone marrow assessment                           | Within 2 weeks of scheduled visit                |
| 28 Days post Treatment Follow-up Form | Haematology/biochemistry assessments, details of medical exam                                                                         | Within 2 weeks of scheduled visit                |
| Adverse Event Form                    | Details of AEs experienced                                                                                                            | Continuous                                       |
| Concomitant Medication Form           | Details of concomitant medications received                                                                                           | Continuous                                       |
| Treatment continuation Form           | Treatment details, haematology/biochemistry assessments and details of medical exam for patients continuing treatment beyond 24 weeks | Within 2 weeks of visit                          |
| Treatment Discontinuation Form        | Date and reason for premature stopping of treatment                                                                                   | Within 2 weeks of stopping treatment             |
| Death Form                            | Date and cause of death                                                                                                               | Immediately upon notification of patient's death |
| Deviation Form                        | Completed in the event of a deviation from the protocol                                                                               | Immediately upon discovering deviation           |
| Withdrawal Form                       | Used to notify the Trials Office of patient withdrawal from the trial                                                                 | Immediately upon patient withdrawal              |
| Event Form                            | Completed when a patient experiences a thromboembolic event of any grade                                                              | Within 2 weeks of resolution                     |

#### Ad hoc forms

Serious Adverse Event Form

Pregnancy Notification Form

This trial will use an electronic remote data capture (eRDC) system which will be used for completion of CRFs.

Access to the eRDC system will be granted to individuals via the Trials Office. SAE reporting and Notification of Pregnancy will continue to be paper-based.

The CRF must be completed by the Investigator or an authorised member of the site research team (as delegated on the Site Signature and Delegation Log) within specified timeframes (listed above and found in the eRDC completion guidelines). The exceptions to this are the SAE Form which must be reviewed and co-signed by the Investigator.

Data reported on each form should be consistent with the source data or the discrepancies should be explained. If information is not known, this must be clearly indicated on the form by selecting e.g. "Not done" where available. Please note this option may not be available for Critical Data Items which are essential to the analysis. All missing and ambiguous data will be queried. All sections are to be completed before returning.

In all cases it remains the responsibility of the Investigator to ensure that the CRF has been completed correctly and that the data are accurate.

Trial forms on the eRDC system may be amended by the Trials Office, as appropriate, throughout the duration of the trial. This will not constitute a protocol amendment.

## 9.2 Archiving

It is the responsibility of the Principal Investigator to ensure all essential trial documentation and source records (e.g. signed Informed Consent Forms, Investigator Site Files, Pharmacy Files, patients' hospital notes etc.) at their site are securely retained for at least 15 years after the end of the trial or following the processing of all biological material collected for research, whichever is the later. Do not destroy any documents without prior approval from the CRCTU Document Storage Manager.

## 10. QUALITY MANAGEMENT

### 10.1 Site Set-up and Initiation

All sites will be required to sign a Clinical Study Site Agreement prior to participation. In addition all participating Investigators will be asked to sign the necessary documents e.g. registration forms, PI Protocol Signature Pages and supply a current CV and evidence of GCP training within the last 2 years to the Trials Office. All members of the site research team will also be required to sign the Site Signature and Delegation Log, which should be returned to the Trials Office. Prior to commencing recruitment all sites will undergo a process of initiation. Key members of the site research team will be required to attend either a meeting or a teleconference covering aspects of the trial design, protocol procedures, AE reporting, collection and reporting of data and record keeping. Sites will be provided with an ISF and a Pharmacy File containing essential documentation, instructions, and other documentation required for the conduct of the trial. The Trials Office must be informed immediately of any change in the site research team.

### 10.2 On-site Monitoring

Monitoring will be carried out as required following a risk assessment and as documented in the CRCTU Quality Management Plan. Additional on-site monitoring visits may be triggered for example by poor CRF return, poor data quality, low SAE reporting rates, excessive number of patient withdrawals or deviations. If a monitoring visit is required the Trials Office will contact the site to arrange a date for the proposed visit and will provide the site with written confirmation. Investigators will allow the TAMARIN trial staff access to source documents as requested.

### 10.3 Central Monitoring

Where a patient has given explicit consent sites are requested to send in copies of signed Informed Consent Forms for in-house review.

Trials staff will be in regular contact with the site research team to check on progress and address any queries that they may have. Trials staff will check completed CRFs for compliance with the protocol, data consistency, missing data and timing. Sites will be sent Data Clarification Forms via the eRDC system requesting missing data or clarification of inconsistencies or discrepancies.

Sites may be suspended from further recruitment in the event of serious and persistent non-compliance with the protocol and/or GCP, and/or poor recruitment. Any major problems identified during monitoring may be reported to Trial Management Group (TMG) and Trial Steering Committee (TSC) and the relevant regulatory bodies. This includes reporting serious breaches of GCP and/or the trial protocol to the main REC) and the MHRA.

### 10.4 Audit and Inspection

The Investigator will permit trial-related monitoring, audits, ethical review, and regulatory inspection(s) at their site, providing direct access to source data/documents.

Sites are also requested to notify the Trials Office of any MHRA inspections.

### 10.5 Notification of Serious Breaches

In accordance with Regulation 29A of the Medicines for Human Use (Clinical Trials) Regulations 2004 and its amendments the Sponsor of the trial is responsible for notifying the licensing authority in writing of any serious breach of:

- The conditions and principles of GCP in connection with that trial or;

- The protocol relating to that trial, within 7 days of becoming aware of that breach

For the purposes of this regulation, a “serious breach” is a breach which is likely to effect to a significant degree:

- The safety or physical or mental integrity of the subjects of the trial; or
- The scientific value of the trial

Sites are therefore requested to notify the Trials Office of a suspected trial-related serious breach of GCP and/or the trial protocol. Where the Trials Office is investigating whether or not a serious breach has occurred sites are also requested to cooperate with the Trials Office in providing sufficient information to report the breach to the MHRA where required and in undertaking any corrective and/or preventive action.

## 11. END OF TRIAL DEFINITION

The end of trial will be the last patient's last visit. The Trials Office will notify the MHRA and main REC that the trial has ended and will provide them with a summary of the clinical trial report within 12 months of the end of trial.

## 12. STATISTICAL CONSIDERATIONS

### 12.1 Definition of Outcome Measures

#### 12.1.1 Primary outcome measure

The primary outcome for the trial is the number of patients who experience a reduction of  $\geq 50\%$  in peripheral blood JAK2-V617F, CALR 5bp insertion (exon 9) or CALR 52bp deletion (exon 9) mutant allele burden at 24 weeks. The primary outcome will be assessed centrally at University of Cambridge. Peripheral blood samples will be sent for patients at baseline and 24 weeks (+/- 4 weeks) which will be compared in parallel for JAK2-V617F or CALR 5bp insertion (exon 9) or CALR 52bp deletion (exon 9) mutant allele burden. If there is a reduction of  $\geq 50\%$  at 24 weeks compared to baseline for either JAK2-V617F or CALR 5bp insertion (exon 9) or CALR 52bp deletion (exon 9), the patient will have met the primary outcome.

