## 3. TRIAL DESIGN

This is a single arm, open label, multicentre, phase II trial of tamoxifen in patients with MPNs.

The aim of the study is to evaluate the activity of tamoxifen in terms of reducing allele burden and the safety of giving tamoxifen in this group of patients. A single stage A'herns design has been chosen to give evidence of activity for the treatment.

All patients will receive a minimum of 24 weeks of treatment with tamoxifen at 20mg od. Patients will be seen at weeks 4, 12, 18 and 24. Mutant allele burden of JAK2-V617F, CALR 5bp insertion (exon 9) and CALR 52bp deletion (exon 9) will be assessed at baseline. Allele burden will be reassessed at 12 weeks and 24 weeks for the mutation(s) identified at baseline. Patients may continue treatment

beyond 24 weeks at the discretion of the treating Investigator. If patients do continue treatment they should be followed up a minimum of 12 weekly and their allele burden reassessed at 36 weeks and 48 weeks as applicable. All patients will be followed up until 28 days after the last dose of tamoxifen treatment.

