#### Blood tests

- Full blood count and biochemistry – please see section 7.2 for full details of tests to include
- Full fasting lipid profile to include triglycerides
- Blood sample collection for **central analysis** of JAK2-V617F, CALR 5bp insertion (exon 9) and CALR 52bp deletion (exon 9) mutant allele burden. Patients must be able to start trial treatment within 6 weeks of this blood sample collection and patients cannot be registered until confirmation of eligibility has been received from the Trials Office that the patient has an allele burden ≥20%.

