### 12.6 Power Calculations

A single stage A'herns design is used to give evidence of activity for the treatment. It is anticipated that no patients on the current treatment will achieve a reduction of  $\geq 50\%$  in allele burden. Given this, if 10% of the patients in this trial were to achieve the required reduction then the treatment would warrant further investigation in a randomised trial. If just 2% of the patients in the trial were to achieve the required level of reduction then the treatment would not be deemed to show any activity that would warrant further investigation. Based on these levels of acceptability and given a one sided alpha of 0.1 and power of 80%, 42 patients would be required for the study. If 3 or more of the recruited patients were to achieve a reduction in allele burden of  $\geq 50\%$  then it can be concluded that the treatment shows a signal of activity and the treatment warrants further investigation in a randomised trial. Patients who die or are lost to follow up prior to the response time point of 24 weeks will be classed as non-responders.

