| Recommendations for assessing treatment-induced cytogenetic and molecular changes |                                                                                                                                                                                                                                                                                                                                                                                                                                                                                                                                                                                                                                                                                  |
| Cytogenetic remission                                                             | At least 10 metaphases must be analyzed for cytogenetic response evaluation and requires confirmation by repeat testing within 6 months window
CR: eradication of a pre-existing abnormality
PR: ≥50% reduction in abnormal metaphases
(partial response applies only to patients with at least ten abnormal metaphases at baseline)                                                                                                                                                                                                                                                                                                                                    |
| Molecular remission                                                               | Molecular response evaluation must be analyzed in peripheral blood granulocytes and requires confirmation by repeat testing within 6 months window
CR: Eradication of a pre-existing abnormality
PR: ≥50% decrease in allele burden
(partial response applies only to patients with at least 20% mutant allele burden at baseline)                                                                                                                                                                                                                                                                                                                                      |

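### The primary responder rule has no per-mutation baseline floor, so a co-mutated patient could count as a responder on a clone below 20% while the qualifying clone does not respond

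*Combined protocol and SAP*

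**What the plan says.** Four parts of the combined protocol and SAP bear on this.

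- **Responder rule (12.1.1).** The primary outcome is a fall of at least 50% from baseline to week 24. With that fall "for either JAK2-V617F or CALR 5bp insertion (exon 9) or CALR 52bp deletion (exon 9), the patient will have met the primary outcome". No minimum baseline burden is attached to the mutation that falls.
- **What is measured (section 3).** All three mutations are tested at baseline. After that, "Allele burden will be reassessed at 12 weeks and 24 weeks for the mutation(s) identified at baseline". The optional plural shows that more than one mutation per patient was foreseen.
- **The 20% floor (4.1, 4.2, 5.1.1, 6).** Central confirmation of a burden of at least 20% is needed before registration. This is a condition on the patient, and one mutation satisfies it.
- **Rationale (1.2.1, 1.2.2).** Measurable disease is defined by a clone of at least 20% for one of the named mutations. The endpoint is presented as a halving of clone size, standing as a surrogate for the drug's effect on the disease.

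Nothing says which mutation decides when a patient has two, or how to class a fall in one alongside no change or a rise in the other.

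**The concern.** Taken literally, the rule gives a co-mutated patient two routes to success. One of them can run through a clone too small to have qualified the patient for the trial. A halving of that clone while the qualifying clone stays put, or grows, is not the event that section 1.2.2 uses to justify the endpoint. Yet it would be scored as a success.

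The decision threshold makes this worth settling. Activity is declared on 3 responders, so one patient classed this way supplies a third of the evidence needed. The error can go only one way: an extra route can add responders and cannot remove any.

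The same definition is used for the 12-week secondary outcome and the 36- and 48-week exploratory outcome. It also enters duration of reduction, where the start (a fall of at least 50%) and the end (reduction below 25%) could be read from different mutations in the same patient.

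**Working it through.** **Inputs from section 12.6**

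- Null rate p0 = 0.02: "If just 2% of the patients in the trial were to achieve the required level of reduction".
- Target rate p1 = 0.10: "if 10% of the patients in this trial were to achieve the required reduction".
- Error rates and size: "given a one sided alpha of 0.1 and power of 80%, 42 patients would be required for the study".
- Decision rule: activity is declared with 3 or more responders.

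**Inputs not in the documents (assumed)**

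- k, the number of co-mutated patients among the 42: 1 to 3.
- q, the chance that such a patient's minor clone halves by week 24 without drug effect: 0.1, 0.3 or 0.5.

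**Step 1: reproduce the plan.** The exact binomial tails are P(X ≥ 3 | 42, 0.02) = 0.0515 and P(X ≥ 3 | 42, 0.10) = 0.805. At n = 41 the power is 0.791, so 42 is the smallest size meeting both limits. The design is correct as stated. Because the achieved type I error is 0.0515 and the planned limit is 0.10, there is some slack. The limit is crossed once the effective null rate exceeds about 2.65%.

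**Step 2: add the second route.** Suppose the qualifying clone responds at the null rate of 2% in every patient, independently of the minor clone. A co-mutated patient is then scored as a responder with probability

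p_m = 1 − 0.98 × (1 − q),

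which is 0.118, 0.314 and 0.510 for q = 0.1, 0.3 and 0.5. The other 42 − k patients respond at 0.02.

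**Step 3: one co-mutated patient.** The tails for the other 41 are P(X ≥ 2) = 0.1977 and P(X ≥ 3) = 0.0486. The type I error is p_m × 0.1977 + (1 − p_m) × 0.0486:

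- q = 0.1: 0.118 × 0.1977 + 0.882 × 0.0486 = 0.0662
- q = 0.3: 0.314 × 0.1977 + 0.686 × 0.0486 = 0.0954
- q = 0.5: 0.510 × 0.1977 + 0.490 × 0.0486 = 0.1246

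Setting this equal to 0.10 gives p_m = (0.10 − 0.0486) / (0.1977 − 0.0486) = 0.345, so q = 1 − 0.655 / 0.98 ≈ 0.33. With a single co-mutated patient, the planned limit holds unless q exceeds about one third.

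**Step 4: more than one.** For general k, sum over j, the number of co-mutated patients scored as responders: C(k, j) p_m^j (1 − p_m)^(k−j) × P(X ≥ 3 − j | 42 − k, 0.02).

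| Co-mutated patients k | q = 0.1 | q = 0.3 | q = 0.5 |
|---|---|---|---|
| 0 | 0.0515 | 0.0515 | 0.0515 |
| 1 | 0.0662 | 0.0954 | 0.1246 |
| 2 | 0.0829 | 0.1582 | 0.2503 |
| 3 | 0.1016 | 0.2366 | 0.4135 |

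**Step 5: with the fix.** If only the qualifying clone counts, every patient is back at 0.02 under the null, and the design returns to 0.0515 and 0.805 with N = 42 and a threshold of 3.

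**The case against.** The strongest reply is that the either/or list in 12.1.1 is there to cover patients with different driver mutations. Read with the measurable-clone definition in 1.2.1 and the clone-size language in 1.2.2, it would mean the mutation the patient was enrolled on. That is a fair account of the likely intent, and it works for any patient with one mutation. It does not settle the patient with two, whom section 3 foresees, and the operative sentence in 12.1.1 says otherwise.

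The second reply is frequency. Section 1.1 reports CALR mutations at 70–84% among patients without JAK2 or MPL mutations, which suggests that co-mutation is uncommon. Nothing in the documents shows that even one such patient will enrol. This stands, and it limits the size of the point.

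Three stronger readings are tempting but not supported.

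- **Type I error of about 0.20.** A reader might take P(X ≥ 2 | 41, 0.02) = 0.198 as the error rate and set it against 0.0515. That figure assumes one false responder is already certain. It is a conditional probability and not the error rate of the rule, and the planned limit is 0.10.
- **Breach of Appendices 6 and 7.** Appendix 6 says that "partial response applies only to patients with at least 20% mutant allele burden at baseline", and Appendix 7 has the same floor. But the floor is worded per patient, and every registered patient meets it. The appendices serve the clinical response outcomes and do not define the primary outcome.
- **Small-clone changes are mere noise.** The documents give no assay precision or detection limit, and the appendices give no reason for their floor. Section 12.1.1 also has the baseline and week-24 samples compared side by side.

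It is also true that 12.3 plans results by mutation type and that allele-burden change is reported. This would help a reader to spot a discordant patient, but it would not change how that patient is counted.

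**Conclusion.** The concern holds as a defect in the wording of the primary responder rule. As written, a co-mutated patient can be a responder on a clone below 20% while the qualifying clone does not respond, which is at odds with the protocol's own rationale for the endpoint.

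Its size depends on two quantities that the documents do not give. With no co-mutated patients the effect is nil. With one, the type I error stays below 0.10 for q up to about 0.33. With two or more it can pass 0.10 at moderate values of q. These figures assume independence between clones and between patients, and a 2% rate for the qualifying clone.

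The sample size calculation is sound and need not change. The case for acting is that the bias is one-sided, the threshold is only 3, and settling a discordant patient after results are known could decide the trial.

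**What to change.** Amend 12.1.1 along these lines: *response is assessed only on a mutation whose centrally measured baseline burden was at least 20%; mutations below 20% at baseline are reported descriptively and do not contribute to response.* Apply the same definition to the 12-, 36- and 48-week outcomes and to duration of reduction, so that the start and end of a response are read from the same mutation.

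If two mutations both reach 20%, the sponsor should state before results are seen which one decides. The mutation with the highest baseline burden is one option. The documents do not favour any particular rule, and what matters is that it is fixed in advance.

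The change uses measurements already planned and leaves N = 42, the threshold of 3 and all single-mutation patients untouched. The cost is a protocol amendment (the amendment table shows that earlier outcome updates were part of substantial amendments) and possibly a slightly lower responder count.
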